**Figure 1 F1:**
[figure not shown]
program evaluation and review technic (PERT) diagram showing flow of participants into cases or non-cases

**Ethical considerations:** ethical approval was obtained from the University of Ibadan/University College Hospital Ethical Committee (Ref: UI/EC/17/0003). Protocol amendments will be communicated to the ethics committee and written approval obtained before commencing. Clinical care providers in the clinic will recruit the participants and obtain assent, then a trained research assistant will obtain informed consent (Annex 1). Anonymized data will be obtained from participants in privacy and data collected will be kept in a secure locked cabinet in an office. Data entered on to the study computer will be password-protected. Personal information will only be recorded in order to send reminders and invitations for follow up sessions. The investigators will have access to the final data set and will not disclose information to other parties.

**Trial registration:** the trial is registered with Pan African Clinical Trial Registry [PACTR201901892865101].

**Reporting of trial results:**Table 1 will describe the demographics of the participants in the intervention and control groups, while Table 2 will show the proportion of cases to non-cases. The changes in these over 6 weeks will be documented in Table 3 and Figure 1. Trial findings will be communicated in a written report to sponsors, presented at a gynecology conference and published in a per-reviewed journal. The authors will be those who have contributed to the conception, design, data acquisition and writing of the manuscript. The full protocol and dataset will be available by contacting the corresponding author.

**Table 1 T1:** distribution of socio-demographic characteristics of participants

Variables	Classes	Intervention group No [%]	Control group No [%]	p-value
Age	< 35 years			
	≥ 35 years			
Marital status	Married			
	Unmarried			
Education	None			
	Primary/ secondary			
	Tertiary			
Occupation	Unemployed			
	Unskilled			
	Skilled			
Previous pregnancies	Yes			
	No			
Identified cause of infertility	Self			
	Male partner			
	Neither/both/ unknown			
Length of infertility	≤ median			
	> median			
Average monthly family income*	≤ median			
	> median			

**Table 2 T2:** participants diagnosed of depression and anxiety by HADS

Variables	Classes	Anxiety				Depression			
		Control group		Intervention group		Control group		Intervention group	
		Cases No. [%]	Non-cases No. [%]	Cases No. [%]	Non-cases No. [%]	Cases No. [%]	Non-cases No. [%]	Cases No. [%]	Non-cases No. [%]
Age	< 35 years								
	≥ 35 years								
Marital status	Married								
	Unmarried								
Education	None								
	Primary/ secondary								
	Tertiary								
Occupation	Unemployed								
	Unskilled								
	Skilled								
Previous pregnancy	Yes								
	No								
Identified cause of infertility	Self								
	Male partner								
	Both/ unknown								
Length of infertility	< median								
	≥ median								
Average monthly family income	< median								
	≥ median								

**Table 3 T3:** comparison of the HADS scores between intervention and control groups at 0, 3 and 6 weeks

	HADS at baseline				HADS at 3 weeks				HADS at 6 weeks			
	Intervention group	Control group	X^2^ test	p-value	Intervention group	Control group	X^2^ test	p-value	Intervention group	Control group	X^2^ test	p-value
Cases												
Non-cases												
Total												

X2 test: Chi square test

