## Abstract

Rationale: high premium is placed on infertility in Nigerian culture. Data is limited on its association with emotional problems in Nigeria. Aims: to develop content for a culturally relevant and cost-effective psychoeducational intervention package and to evaluate its effectiveness for reducing symptoms of anxiety and depression. Sample size estimate: Methods and design: a multi-method study design including development and validation (which includes focus group discussions) of an audio-visual tool which will serve as the intervention in a randomized controlled trial. Data will be analyzed with interim and survival analyses. Population studied: one hundred and 138 (68 per group) infertile women attending infertility clinic in Ibadan. Study outcomes: anxiety and depressions scores assessed with the hospital depression and anxiety scale (HADS) at 0, 3 and 6 weeks. Discussion: it is hoped that the use of the audio-visual tool will improve participants depression and anxiety scores and that the tool will be used for education in routine clinic use and community awareness on psychosocial effects of infertility.

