
### Phase II: randomized controlled trial to test the effectiveness of the psychoeducational intervention

**Study design:** a randomized controlled trial with an allocation ratio of 1: 1 will be utilized.

**Study setting:** 1) University College Hospital (UCH), Ibadan, Nigeria: it serves as a referral tertiary center for Nigeria and sub-Saharan Africa. The study will be at the outpatient gynecology clinic of the hospital; 2) Adeoyo Maternity Hospital (AMH), Yemetu, Ibadan, Nigeria: this is a province-owned secondary health care facility.

**Study subjects:** women attending gynecology clinics in UCH or AMH on account of infertility. Consenting participants will be randomized into the intervention and control arms of the study, respectively.

**Eligibility criteria:** women aged 18 years and above, who have been trying to conceive for at least one year, and who do not have any children.

**Interventions:** consecutive, eligible infertility clinic attendees will be invited to participate in the study and informed consent obtained. Sociodemographic data would be collected via a structured questionnaire. Baseline assessment on participants' psychological and emotional state will be collected via Hospital Anxiety and Depression Scale (HADS) [28]. Thereafter, the participants will be allocated into study groups. Participants in the intervention arm will attend the intervention session on a specified date at the facility. The psychoeducational video will be viewed, and immediate feedback will be obtained. Participants in the control arm will also receive the usual treatment offered all attendees at the gynecology clinics - comprising health talks by public health nurses and explanations and counselling provided by the managing physicians. The study´s primary outcomes are depressive and anxiety symptoms. HADS is a self-assessment scale which has subscales that measure severity of anxiety and depression. It is validated for use in medical outpatient clinics. Participants are followed up at three and six weeks; HADS will be administered at both times. Participants will be counseled on the need for follow-up. Recruited respondents in both arms will receive phone call reminders ahead of scheduled clinic appointments to improve attendance and minimize loss to follow-up.

**Sample size estimation:** the minimum sample size was determined using the formula for comparing two means i.e.

$$\text{n=}\frac{2{\left[Z_{1-\alpha /2}+Z_{1-\beta }\right]}^{2}}{\Delta^{2}}$$

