where Δ, effect size =

$$\Delta =\frac{\mu_{1}-\mu_{1}}{\sigma }$$

where Z1-α/2 [α] was set at 5% i.e. 1.96; Z1-β [β] was set at 20% i.e. power at 80% = 0.84 [29]. A moderate effect size of 0.53 was used. A minimum sample size of 57 was calculated. Attrition rate of 20% was incorporated in the calculation and sample size was estimated at 68 women in each group.

**Randomization procedure:** a randomization list of randomly permuted blocks of treatment assignments in blocks of 4 will be prepared by the study statistician, using a computer-generated table of random numbers. The research assistant will open the sealed envelope containing the assigned group after baseline HADS has been administered. The clinical staff recruiting participants and the data analyst will be blinded, as he will receive two spreadsheets of data without knowing which is the intervention arm.

**Data management and analysis:** the data collected will entered into the computer and analysed using IBM SPSS version 23.0. Interim analysis will be carried out using Mann-Whitney-U test to compare independent samples of the intervention and control groups at 0, 3 and 6 weeks. Survival analysis will also be carried out at each time to assess number of cases of depression or anxiety that transited to non-cases (Figure 1). A data monitoring committee is not necessary as there are no interventions bordering on patient safety. There are no issues that might necessitate termination of trial. Malfeasance or adverse events are not applicable in a trial that constitutes audiovisual expert education as the intervention.

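### Table 3 is titled a comparison of HADS scores but holds only undivided case/non-case chi-square tests, at odds with the score outcomes, the two-means sample size and the Mann-Whitney test, and the article does not say which result counts

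*Protocol article*

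**What the plan says.** Four parts of the Protocol article treat the outcome as a score:

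- The Abstract gives the outcomes as "anxiety and depressions scores assessed with the hospital depression and anxiety scale (HADS) at 0, 3 and 6 weeks".
- Under Phase II, Interventions, the "primary outcomes are depressive and anxiety symptoms", and the instrument is described so: "HADS is a self-assessment scale which has subscales that measure severity of anxiety and depression".
- Under Sample size estimation, "the minimum sample size was determined using the formula for comparing two means", with a standardised effect of 0.53, two-sided alpha of 5% and power of 80%. This gives 57 per group, raised to 68 for attrition.
- Under Data management and analysis, an analysis labelled interim is to be done "using Mann-Whitney-U test to compare independent samples of the intervention and control groups at 0, 3 and 6 weeks".

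Other parts treat it as case status:

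- Data management and analysis adds a survival analysis of cases that become non-cases.
- Reporting of trial results says that Table 2 gives the proportion of cases to non-cases, and then: "The changes in these over 6 weeks will be documented in Table 3 and Figure 1".
- Table 3 is titled "comparison of the HADS scores between intervention and control groups at 0, 3 and 6 weeks", but has only the rows Cases, Non-cases and Total, one HADS block per visit, and a test column explained in the footnote as "X2 test: Chi square test".

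Table 2 has separate Anxiety and Depression blocks. Table 3 does not.

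**The concern.** Table 3 disagrees with its own title and with the basis on which the trial was sized. It has no cell for a mean, a median or a difference between arms. Neither of the other planned tables fills the gap: Table 1 is demographic, and Table 2 breaks case status down by demographic class, without visits or tests. The outcome used for the sample size therefore appears in none of the three tables.

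Two further points follow. First, a single Cases row does not say whether a case is a woman with anxiety, with depression, with either or with both, although these are two primary outcomes. Second, the text names a rank test and the table a chi-square test at the same three visits, with no statement of which carries the conclusion. The two can disagree, and cutting a score into case and non-case discards information. A reader of the results would not know which comparison had been chosen in advance, and one of the two candidates has much less power for the effect that the trial is meant to detect.

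**Working it through.** **Inputs from the article:** effect 0.53 SD; z values 1.96 and 0.84; 57 per group before and 68 after the attrition allowance; attrition 20%.

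**Inputs assumed:** the article gives no HADS cut-off, case rate, mean or SD. I take a normal score, a pure shift of 0.53 SD, and control case rates from 20% to 60%.

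**1. The plan's own figure.** n = 2(1.96 + 0.84)² / 0.53² = 15.68 / 0.2809 = 55.8, so 56 per group. The article states 57, which agrees to within rounding. The calculation is for a comparison of mean scores.

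**2. Number analysed.** 68 × 0.8 = 54.4, so 54 per arm if the allowed attrition occurs.

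**3. Power for scores at 54 per arm.** Φ(0.53 × √(54/2) − 1.96) = Φ(2.754 − 1.96) = Φ(0.794) = 0.786. This is the normal approximation for a comparison of means. For the Mann-Whitney test that the text names, simulation gives about 75% to 76%, and the approximation with relative efficiency 3/π gives 77%. The range for a score analysis is therefore about 75% to 79%.

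**4. Power for case status at 54 per arm.** With control case rate p₁, the cut-off lies at z(1 − p₁), and the same shift gives p₂ = 1 − Φ(z(1 − p₁) + 0.53). With p̄ = (p₁ + p₂)/2:

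power = Φ{ [(p₁ − p₂)√n − 1.96√(2p̄(1 − p̄))] / √(p₁(1 − p₁) + p₂(1 − p₂)) }

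Example at p₁ = 0.50: p₂ = 1 − Φ(0.53) = 0.298 and p̄ = 0.399. The numerator is 0.202 × 7.348 − 1.96 × 0.6925 = 0.127 and the denominator is 0.678. Φ(0.187) = 0.574.

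| Assumed control case rate | Implied intervention rate | Chi-square power, 54 per arm | Chi-square power, 57 per arm | n per arm for 80% power |
|---|---|---|---|---|
| 20% | 8.5% | 40% | 42% | 145 |
| 30% | 14.6% | 49% | 51% | 114 |
| 40% | 21.7% | 54% | 56% | 99 |
| 50% | 29.8% | 57% | 60% | 92 |
| 60% | 39.1% | 59% | 61% | 89 |

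**5. Sensitivity.** Over control case rates from 10% to 80%, chi-square power at 54 per arm never exceeds about 59%, and it falls to 27% at a 10% rate. With all 68 per arm analysed, the maximum is about 69%, against 87% for a comparison of means.

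**The case against.** The strongest reply is that the article does plan a score-based test, at the same visits as Table 3, and that the case content of the table is deliberate: the reporting paragraph says that the table follows changes in case proportions. On that view the title is a slip, Table 3 is only an empty shell, and further shells can sit in the full protocol or the analysis plan.

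Much of this stands. A reader might infer from Table 3 that the trial will be judged on a dichotomised outcome. The article does not support that: no sentence makes the chi-square test primary or decisive. Nor does the undivided Cases row show that anxiety and depression will be pooled. It may be a compressed layout, and Figure 1, its companion display, cannot be seen here. The power figures also rest on case rates that the article does not supply, and against the Mann-Whitney test at case rates of 50% to 60% the loss is about 16 to 19 points, not more.

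What does not fall away is the conflict in the printed text. The score test is called interim and has no place in the planned tables. The chi-square test is in the table but absent from the analysis text. A corrected title alone would leave open which of them counts, and would leave the scores without a table.

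**Conclusion.** The point holds as an internal conflict that needs to be settled. Table 3 does not match its own title, the two score-based primary outcomes, the two-means sample size or the test named in the text; it does not identify the subscale; and the article does not say which result is the main one.

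The cost in power is conditional. It arises only if the chi-square result is the one relied on. In that case a true effect of the planned size would be missed about 41% to 60% of the time at 54 per arm, compared with about 21% to 25% for a score analysis. These figures assume a normal score, a pure shift of 0.53 SD, 20% attrition and control case rates of 20% to 60%. The size of the loss varies with those assumptions. At no case rate tried, from 10% to 80%, does the chi-square test approach the stated 80% at the planned sample size.

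**What to change.** 1. In Data management and analysis, state that the between-arm comparison of HADS-Anxiety and HADS-Depression scores is the main analysis, and no longer present it only as an interim one.
2. Redraw Table 3 with one panel per subscale: number of women and score summary (mean and SD, or median and interquartile range) by arm at 0, 3 and 6 weeks, with the between-arm difference and its 95% confidence interval at 3 and 6 weeks.
3. Report case proportions by arm and visit, split by subscale, as a secondary display under a title that says so.

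The cost is one table shell and one sentence. HADS is already collected at all three visits, so no new data are needed.
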